#### Final session

The final session offers a chance for the couple to review their progress in meeting their goals. No new skills or topics are introduced; rather, the counselor reviews their progress from the first session through to the final one. They discuss whether they met their goals with regard to any decisions regarding HIV testing or other HIV-related issues. The couple then discusses any challenging upcoming events that may be in their future and discuss strategies to use the skills they have used to meet them. They discuss the resources that they have identified in their community and the skills that they have learned. The final exercise is an exploration of their commitment to each other. The counselor assists them with identifying actions they can do for their partner to demonstrate their love and commitment to each other. Couples receive a certificate of completion.

All four couples’ counseling sessions have to be completed within 90 days post-randomization.

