#### Primary outcome: sexual behavior

In addition to CHCT, our intervention is designed to reduce sexual risk behavior for HIV. We hypothesize that:

1) During follow-up, intervention participants will report fewer acts of unprotected sexual intercourse with: a) primary sex partners; and b) outside sex partners, relative to participants in the control group.

2) During follow-up, intervention participants will report fewer concurrent outside (that is, secondary) sex partners relative to participants in the control group.

We will test longitudinal hypotheses using random effects models to examine changes in participant trajectories in sexual risk outcomes. These longitudinal analyses will treat the individual as the unit of analysis and will include an additional random intercept to account for within-couple response correlations. Initial analyses of sexual risk behavior will follow an ITT approach and include intervention group assignment, time of measurement, and an intervention group-by-time interaction term.

It is critical to optimize the accurate reporting of self-reported sexual risk behavior given its role as a primary outcome of our trial. To account for any possible bias, we have taken the following precautions: 1) we are using previously validated instruments; and 2) the assessment and intervention activities are conducted by different staff members. Thus, we do not expect any differential effects of social desirability reporting across arms of the study.

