#### Power analysis

With projected attrition of 20% due to break-ups and 10% due to other causes, we require 350 couples to be randomized in order to achieve the sample size target at 9 months of 245 couples at the final 9-month follow-up. As stated, our primary outcome is determined for only the final follow-up time point, and not for any other group differences at other intervention time points (for example, between first and second group session). The actual prevalence of couple HIV testing is unknown. Thus, for the proposed logistic regression analyses we computed the minimum detectable odds ratio assuming a low prevalence of couple HIV testing (10%) and a medium prevalence of couple HIV testing (30%). For these scenarios, the minimum detectable odds ratios were 2.85 and 2.18, respectively. This was calculated for 80% power. Given the resource-intensiveness of this study intervention, we believe a substantial odds ratio is needed to merit rollout of such an intervention on a public health scale. For time to couple HIV testing survival analyses, under the same assumptions, the minimum detectable hazard ratios are 2.70 and 1.77.

For our sexual behavior outcomes, the minimum detectable R^2^ values fall below 1% for this continuous variable, which is considered a ‘small’ effect size according to Cohen’s [62] criteria for the R^2^ statistic. We based our calculations on data which reported a base rate of 2.35 unprotected sex acts per 3 months (from the study by Genberg and colleagues [6]). We have 80% power to detect a reduction in the mean number of unprotected sex acts from a base rate of 2.35 to 2.04 or 2.12 depending upon the level of within-participant correlation of reported sex acts over time.

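### The sexual-risk hypothesis concerns a mean level during follow-up, but the analysis is framed on trajectories with a group-by-time term and states neither a follow-up mean contrast nor baseline adjustment

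*Protocol article*

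**What the plan says.** The protocol article makes sexual risk behaviour one of two primary outcomes. Under the heading Primary outcome: sexual behavior, the first hypothesis is a level: "During follow-up, intervention participants will report fewer acts of unprotected sexual intercourse with" primary and outside partners, relative to control. The second hypothesis, on concurrent outside partners, has the same form.

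The analysis in that section is framed on change. Hypotheses will be tested "using random effects models to examine changes in participant trajectories in sexual risk outcomes". The models "will treat the individual as the unit of analysis and will include an additional random intercept to account for within-couple response correlations". The initial intention-to-treat analyses will "include intervention group assignment, time of measurement, and an intervention group-by-time interaction term". The text does not say which term or contrast decides the hypothesis, how time is coded, or whether baseline enters as a response or as a covariate.

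Power analysis again refers to a level: "We have 80% power to detect a reduction in the mean number of unprotected sex acts". The starting value there is 2.35, and two detectable means are given, 2.04 and 2.12, according to how strongly one person's repeated reports are correlated. The Design section gives surveys at 3, 6 and 9 months, in addition to the baseline survey. On delivery, the section Final session says the four counselling sessions "have to be completed within 90 days post-randomization".

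**The concern.** A difference in level and a difference in trajectory are separate quantities. Since counselling must end at about the time of the first follow-up, an effect that is present at month 3 and then held is a plausible shape. A linear interaction picks up such a step poorly. Fitted to months 3, 6 and 9 alone, it has no power beyond alpha, because the arms run parallel. An analyst who takes the interaction as the test could then report no differential trajectory even though the intervention arm is lower at every follow-up.

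The stated terms also do not use the baseline count in the most efficient way. Baseline is measured before randomisation, so the true difference between arms at that point is zero. A model with baseline as a response and a free group effect spends information on estimating that difference.

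This goes beyond normal condensation in an article. For couples testing, the same article names the test (chi-square) and says which comparison is primary. For sexual behaviour it states an analysis framework that does not line up with its own hypothesis.

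**Working it through.** **Inputs from the article.** Base rate 2.35; detectable means 2.04 and 2.12; 80% power; 245 couples at 9 months, so 490 individuals and 245 per arm; 1:1 allocation; visits at 0, 3, 6 and 9 months.

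**Assumed, because not given.** Two-sided alpha 0.05; Poisson variance at the average of the two rates; compound symmetry with within-person correlation r; no between-partner correlation.

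**Step 1: which test underlies 2.04 and 2.12?** Let V be the variance factor of a contrast. The figures require V = Δ² × 245 / [(1.96 + 0.8416)² × 2σ²].

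- For 2.04: Δ = 0.31, 2σ² = 4.39, V = 0.683.
- For 2.12: Δ = 0.23, 2σ² = 4.47, V = 0.369.

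Solving each contrast for r, with a sustained effect for the slope:

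| Contrast | V | r for 2.04 | r for 2.12 |
|---|---|---|---|
| Mean of 3 follow-ups | (1+2r)/3 | 0.52 | 0.05 |
| Mean of 4 waves | (1+3r)/4 | 0.58 | 0.16 |
| Follow-up mean minus baseline | 4(1−r)/3 | 0.49 | 0.72 |
| Linear group-by-time slope, 0 to 9 months | (1−r)/0.45 | 0.69 | 0.83 |

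Every row gives an admissible r, so the published figures do not identify the test.

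**Step 2: power if the effect is sustained from month 3.** Scale the effect to 80% power for the unadjusted follow-up mean. Then power = Φ(2.802 × √ratio − 1.96), where ratio = [(1+2r)/3] / V. For the baseline-adjusted mean, V = (1+2r)/3 − r².

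Worked at r = 0.5:
- The unadjusted mean has V = 0.667.
- The slope has V = 0.5/0.45 = 1.111, ratio 0.600, and power Φ(0.210) = 58%.
- The adjusted mean has V = 0.417, ratio 1.600, and power Φ(1.584) = 94%.

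| r | Linear interaction | Post-versus-baseline interaction | Baseline-adjusted mean |
|---|---|---|---|
| 0.05 | 21% | 33% | 80% |
| 0.3 | 37% | 56% | 87% |
| 0.5 | 58% | 80% | 94% |
| 0.7 | 87% | 98% | 99% |

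**Step 3: adjusting versus differencing.** The difference in variance factors is 4(1−r)/3 − [(1+2r)/3 − r²] = (1−r)², which is never negative. Adjusting cuts the variance by 71%, 53% and 38% at r = 0.05, 0.3 and 0.5 (for example, at 0.5, 1 − 0.417/0.667 = 37.5%).

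**Step 4: a growing effect.** Let one third, two thirds and all of the Step 2 effect be present at months 3, 6 and 9. The slope ratio becomes (5/9)/(1−r) × (1+2r)/3, and the adjusted-mean ratio (4/9) × [(1+2r)/3] / [(1+2r)/3 − r²].

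- r = 0.05: slope 25%, adjusted mean 47%.
- r = 0.3: 45% and 54%.
- r = 0.5: 67% and 66%.
- r = 0.7: 93% and 85%.

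The advantage over the slope is gone near r = 0.5 and reversed at 0.7.

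**The case against.** The strongest reply is that the article says only that the model will include the interaction. It does not call it the sole or deciding test, and with categorical time the same model yields a follow-up mean contrast. Time coding, contrasts and covariates are often left to the analysis plan. This stands in part. A reader might infer that the protocol commits to testing the hypothesis by the interaction alone, and the text does not support that. What remains is that the only framing given is trajectories, and it does not match the hypothesis as worded.

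Second, a reader might infer that 2.04 and 2.12 fit only a comparison of follow-up means, so that the power statement itself contradicts the model. Step 1 shows otherwise: interaction contrasts reproduce both figures at other correlations, and the article gives no SD, correlation or alpha to choose between them.

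Third, the step shape is not certain. The month-3 report covers the preceding three months, when sessions are still being delivered, and couples may take up testing at any time to month 9. A growing effect is therefore credible, and Step 4 shows what it does to the comparison. The lowest power figures need linear time, a pure step and low correlation together. At r = 0.5 the post-versus-baseline interaction already has 80%.

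Finally, a group-by-time model of change is a valid analysis. The issue is its match to the hypothesis and its efficiency, not bias.

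**Conclusion.** The point holds as a mismatch between the hypothesis and the stated analysis framework on a primary outcome. It does not hold as an error in the power figures. If the interaction is taken as the test and the effect is sustained, power is about 21% to 58% for r from 0.05 to 0.5, against 80% to 94% for the baseline-adjusted mean. This rests on compound symmetry, linear time and a step effect.

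The general statement that the adjusted mean always has far more power than the slope is not supported. The gain shrinks as correlation rises and can reverse for a growing effect. The advantage of adjusting over differencing from baseline holds at every correlation.

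Overdispersion and between-partner correlation, for which the article gives no values, would change the absolute figures. Partner correlation drops out of the slope but not wholly out of the follow-up mean, so allowing for it would narrow that gap somewhat. The change should be made, but the planned model is not invalid without it.

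**What to change.** State the deciding contrast for sexual risk as the intervention-control difference averaged over months 3, 6 and 9. Take it from a mixed model with categorical time, the baseline count as a covariate (or baseline means constrained equal across arms), and the planned random intercepts. Report the group-by-time interaction as secondary, to describe whether the effect grows or fades. In the power section, give the SD, correlation, alpha and contrast behind 2.04 and 2.12.

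This is a change of wording and needs no new data. The price is some loss of power, relative to a slope test, against a slowly growing effect when within-person correlation is high: 85% against 93% at r = 0.7 in Step 4.

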#### Power analysis

With projected attrition of 20% due to break-ups and 10% due to other causes, we require 350 couples to be randomized in order to achieve the sample size target at 9 months of 245 couples at the final 9-month follow-up. As stated, our primary outcome is determined for only the final follow-up time point, and not for any other group differences at other intervention time points (for example, between first and second group session). The actual prevalence of couple HIV testing is unknown. Thus, for the proposed logistic regression analyses we computed the minimum detectable odds ratio assuming a low prevalence of couple HIV testing (10%) and a medium prevalence of couple HIV testing (30%). For these scenarios, the minimum detectable odds ratios were 2.85 and 2.18, respectively. This was calculated for 80% power. Given the resource-intensiveness of this study intervention, we believe a substantial odds ratio is needed to merit rollout of such an intervention on a public health scale. For time to couple HIV testing survival analyses, under the same assumptions, the minimum detectable hazard ratios are 2.70 and 1.77.

For our sexual behavior outcomes, the minimum detectable R^2^ values fall below 1% for this continuous variable, which is considered a ‘small’ effect size according to Cohen’s [62] criteria for the R^2^ statistic. We based our calculations on data which reported a base rate of 2.35 unprotected sex acts per 3 months (from the study by Genberg and colleagues [6]). We have 80% power to detect a reduction in the mean number of unprotected sex acts from a base rate of 2.35 to 2.04 or 2.12 depending upon the level of within-participant correlation of reported sex acts over time.

## Discussion

The Uthando Lwethu intervention is the first couples-based intervention to have CHCT as its outcome, an approach that has been advocated but not yet implemented widely [16]. The intervention is a theory-based relationship-focused intervention that emphasizes the improvement of positive relationship dynamics and communication skills as they are hypothesized to be the mechanisms by which couples choose to engage in CHCT and reduce sexual risk for HIV. Motivations to participate in couples-based testing for HIV are relationship-focused [18]. Partners want to establish trust, demonstrate commitment to each other, and know their HIV status prior to embarking on future decisions such as having children together, or getting married [18]. Prior attempts at couples-based approaches to HIV prevention have more often utilized individually-focused theoretical orientations, thereby neglecting the influence that partners play in decisions around HIV, both its prevention and potential transmission [9,63].

Improving rates of CHCT is a high leverage outcome which has the potential to improve rates of testing, disclosure, sexual risk reduction, and treatment initiation for heterosexual couples in a rural area of South Africa which is highly impacted by HIV. While CHCT has been shown to be efficacious for sexual risk reduction, uptake has been low in South Africa. Our strategies are aiming to address factors that may have contributed to the historically low uptake of CHCT. For example, we are utilizing a community-based approach, which is likely to increase our access to and participation of men; we are taking our services to where men are, as opposed to prior work with couples that has been conducted mostly in the context of clinic-based environments (for example, PMTCT interventions). Other innovations include the use of mobile caravans for provision of counseling services, intervention activities and CHCT, and the use of mobile phones for data collection.

Uthando Lwethu integrates relationship-focused education and skills training into an HIV-focused couples-based intervention. In addition, it incorporates relationship education approaches [44,60] and interdependence theory [40] to increase positive relationship dynamics. By specifically targeting relationship commitment, intimacy, and satisfaction we are directly intervening in the context of HIV risk in South Africa, that is, primary relationships. Thus, our intervention has the aim of both increasing CHCT (thus increasing mutual knowledge of serostatus), reducing sexual risk behavior for HIV with both primary and secondary partners (perhaps in the absence of knowledge of serostatus), and improving our understanding of how relationship issues influence these behavioral choices. This represents an attempt to move away from individual-level approaches, to a more integrated approach for HIV prevention.

Couples-based interventions for HIV, including those that target testing and sexual risk reduction have been identified as a high priority [11,38,63]. CHCT necessitates the testing and mutual disclosure of both partners, conditions that are essential for improving subsequent outcomes such as sexual risk reduction and improving treatment outcomes. Although interventions aimed towards improving rates of testing for male partners of antenatal clinic attendees have had similar goals, they have reported mixed results [64,65].

We will learn from our intervention whether conducting a couples-based, relationship-focused intervention is feasible in a context which presents unique challenges for couples, for example, low rates of marriage, high rates of mobility. Should the intervention demonstrate efficacy, next steps could include a rollout of this public health intervention, as well as adapting and testing our approach for couples who are experiencing current intimate partner violence, substance use, or pregnant women.

Heterosexual couples in this context are at high risk for HIV infection, and engaging in CHCT could garner positive outcomes for primary and secondary prevention as well as treatment outcomes [11] (for example, earlier ART initiation, reduced HIV transmission risk stemming from early ART, access to PrEP, and so on), which can significantly impact public health outcomes in this community. Mutual disclosure of serostatus can also improve social support and relationship quality, in addition to facilitating successful sexual risk reduction. The results of our ongoing clinical trial will provide much needed information regarding whether a relationship-focused approach is effective in increasing rates of participation in CHCT. Choosing to engage in CHCT represents a crucial decision for couples with significant implications for their psychological and physical welfare. Our results will indicate whether this decision can be facilitated by providing couples with skills to improve their communication not only about their sexual behavior and decisions, but about the relationship context in which these decisions take place.

## Trial status

Recruitment for the trial began in March 2012 and will continue through 2014. As of June 2013, we have enrolled 155 couples.

## Abbreviations

ART: Antiretroviral therapy; BMT: Behavioral marital therapy; CAB: Community Advisory Board; CDC: Centers for Disease Control and Prevention; CHCT: Couples-based HIV counseling and testing; DSMB: Data Safety and Monitoring Board; ITT: Intention-to-treat; PI: Principal investigator; PMTCT: Prevention of mother-to-child transmission; PReP: Pre-exposure prophylaxis; PREP: Prevention and Relationship Enhancement Program; QA: Quality assurance; RCT: Randomized controlled trial; STI: Sexually transmitted infection; TB: Tuberculosis; WHO: World Health Organization.
